#### Sampling procedure

As highlighted in Table 3, it is anticipated that a total of 570 respondents will be interviewed at national, district, and facility levels. The sampling approach for these respondents will be based on two orders. Figure 3 illustrates the sampling stages and the randomization in the questionnaire administration.

**Fig. 3 Fig3:**
[figure not shown]
The selection flow of respondents

##### First-order respondents

This includes respondents that are involved in or close implementation of the policy activities and hence they will be purposefully identified at the three levels. For example, at the national level, the first-order respondents will be those with formal mandate for implementing the selected policies – i.e. programme officials and national committees for 1) Malaria Control Programme and 2) Maternal and Child Health and Family Planning, and district level respondents will comprise the district health management teams (DHMT) and from the selected health facilities.

##### Second-order respondents

For each selected policy, a stakeholder mapping will be embedded in the interview (module 2) to identify the key stakeholders at national, district and facility level that are involved in or closer to the implementation of the selected policies. The respondents from this order will be identified by the first-order respondents. The most critical consideration in the selection of second-order respondents is that they must be engaged in an essential way in the implementation of the selected policy or programmes activities and be listed at least twice among the first-order respondents. Organisations mentioned/listed more than twice will form the sampling frame for the second-order interviews and 20 of these will be approached for barometer interviews.

Module 2 also collects information about the main roles played by these stakeholders.

Overall the anticipated sampling frame will include: MOH programme officials; National programme officials; district managers including (district Health Management Team (DHMT) and managers of district programmes that support the selected policy areas (malaria emergency obstetric care and family planning); Non-DHMT respondents will be identified by way of a rapid district level mapping of organisations that support these policy areas and this will be conducted with the guidance of the district health office (DHO) (module 2 on organisational networks). For each district, interviews will be conducted at one hospital (referral or general hospital), one Level IV health center and two Level III health centers, and two Level II health centers. This sample frame and procedures will reflect both the public and private facilities in the selected district. Where the numbers of facilities exceed those required for the sample, we will do stratified sampling within each level of facilities.

For objective 5, we plan to learn from the process of dissemination of the PIB findings. The main methods of data collection will involve the active documentation of stakeholder reactions and responses to the findings. The questions they ask about the finding and the ideas they propose about PIB and about corrective actions to improve implementation of the policy programmes. We aim to organise 2–3 dissemination meetings, and 2–3 focused dialogues with sub-groups of stakeholders on key issues that emerge from the PIB. We will use a structured narrative to capture the main aspects of responses to the PIB findings. In cases in which dissemination happens using mass media (radio, TV), we will also note the comments and questions raised and or the proposed ideas from the media/public. These will be analysed and used to improve the PIB tool and to produce an “ideas brief” that will complement the barometer findings. The brief will be shared with the target group and also help in interpreting findings or making plausible recommendations.

#### Questionnaire administration – On-line and face-to-face interviews

Through the two identified approaches, we seek to compare the on-line and face-to-face administration of the PIB questionnaires among the target groups. The purpose is to find the most effective way to interview respondents at the national, district and facility levels for the PIB. To inform future barometer surveys and to generate panel data to track trends in the key implementation domains, we will compare response rates, interview completeness and costs between on-line and face-to-face. A pool of respondents and their telephone contact at each level (national, district and facility) will be generated. From Table 3 half of the respondents will be assigned to either face-to-face or on-line interviews. Those that are assigned to fill on-line questionnaires will be requested to provide email addresses so that they can be invited to participate in the study. Within the email, a web-link to the survey will be provided. The survey will be hosted on the MakSPH server. To compensate respondents for the data and connectivity costs of filling the survey, a token of appreciation will be provided.

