There is limited research that tracks the implementation phase of policies for the benefit of informing corrective actions [1, 2]. This gap manifests in delayed corrective actions for policy implementation processes or gradual abandonment of policies that would otherwise transform the health and welfare of communities. Although some programme monitoring tools exist, these mostly serve a technocratic objective, mostly organised on the basis of project silos and internal indicators of project management. Evidence emerging from HIV programmes show that active implementation tracking of project indicators has a tendency to divert the health systems capabilities towards a couple of projects to the neglect of other vital policy programmes [5].

The specific objectives of the PIB study are (1) To assess the perceived appropriateness of policy programmes implemented to address identified policy problems (e.g. policy goals, strategies, standards and processes of decision making); (2) To assess, using priority parameters, the extent to which the prerequisites for implementation are established (e.g. awareness of policy objectives, resources provision, network of role bearers, community demand, policy champions); (3) To determine the enablers and constraints to implementation of the selected policies (e.g. workforce, finance, and medicines and the interdependencies of action network); (4) To compare on-line and face-to-face administration of the PIB questionnaire among target respondents (ease of access, response rate, costs); and (5) To document stakeholder responses to PIB findings with regards to policy implementation, awareness and actions. This will include dialogue on content such as implications and recommendation, actionable findings and role accountability collaborative actions.

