### Study design

There will be three PIB waves. The first wave is the initial situation analysis survey which will assist the implementation of policies in the project’s lifespan. The second wave will be conducted in the third year of the project and the last wave will be final evaluation. Data collection will utilise the same tools and approaches in order to capture any changes hence, this PIB will be a longitudinal survey where both qualitative and quantitative data collection methods will be employed. The PIB study will be descriptive and analytical by focusing on selected policy cases with multiple assessment domains as outlined in Fig. 2.

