##### Quantitative data

The likert scale-type options will be used for key measures of implementation status. The three questionnaires covering the three policy domains of family planning, malaria and emergence obstetric care (annexes 1, 2 and 3) are structured to include issues of policy resources, policy standards, implementation processes and other contextual factors that mediate policy implementation, which are further summarised in Table 4 as a framework for organising the assessment of the policy domains. Each questionnaire has six modules and addresses objectives 1 to 3. The first module is about policy specific details i.e. the policy objectives, and related programmes and plans that guide the implementation. The programme activities were used to generate six generic modules for assessment in Fig. 2. In the first module, all the selected policies will be assessed on the basis of their unique policy aspects.

**Table 4 Tab4:** Framework for organizing the assessment domains for the- first wave of Policy Implementation Barometer

All Policy domains	Level of analysis	Policy resources (inputs)	Policy standards (process)	PIB indicator categories	Data sources
1. Family Planning 2. Malaria 3. Emergence obstetric care	Macro level	Availability of: • financial resources; • human resources (admin and technical staff); • other resources (equipment, supplies, medicines, etc.); • implementing agencies	Availability of: • regulations, • technical guidelines, • Standard Operating Procedures (SOPs); • Communication plan; • Enforcement mechanisms (normative, remunerative or coercive); • Policy champion; • Political resources (oversight committees, etc.); • Reporting structures and mechanisms	• Resources and services indicators • Community engagement indicators • Integration and responsiveness indicators • Family planning indicators • Malaria program coverage indicator *Emergency obstetric care* • Emergency obstetric care indicators • Policy champion; • Political resources (oversight committees, etc.); • Reporting structures and mechanisms	• Documents review • Key informant interviews • Interviews with implementers (all levels) • Secondary data (studies, surveys, routine health information, etc.
	Meso level	Same as above	Same as above	Same as above	Interviews Routine data
	Micro level	Facility level data - similar to the above	Facility level guidelines, SOPs, etc.	Facility level	Interviews Routine data

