### Data analysis and displays

All quantitative and qualitative data collected from secondary and primary sources will be used to construct the barometer measurement metrics for the selected policies or policy domains. Descriptive and comparative statistics will be calculated to show implementation progress by policy/programmeme areas. The analysis will be simple enough to be understood by decision makers but clear enough to show actual implementation gaps. Qualitative data collected through open-ended questions, will be analysed using the conventional content analysis (CCA) to establish the main underlying factors contributing to implementation of specific policies.

All indicators will be tested for validity and reliability and most importantly for the ease with which they can be generated using routine and administrative data. A dashboard or score card will be developed to display performance or progress of the first wave barometer assessment. Simple info-graphics will be developed in ways that allow for easy updates and analysis of future trends.

The value of a well-functioning PIB is that it may extend the value chain and transcend the current health issues, thus adding ‘forecasting’ to the (A) Prevention, (B) Treatment, and (C) Follow up chain. This includes identification of and planning for future health issues and using the barometer to measure the country’s effectiveness in terms of addressing them.

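### The on-line versus face-to-face comparison leaves out the Likert scores, so a mode could be chosen for later waves without checking that it gives the same scores

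*Protocol article*

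**What the plan says.** The outcomes of the mode comparison are listed in two places in the protocol article. The section on questionnaire administration says "we will compare response rates, interview completeness and costs between on-line and face-to-face". Objective 4, as given under Purpose, lists "ease of access, response rate, costs". The later list of specific objectives repeats the objective without naming outcomes.

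The same questionnaire section gives the reason for the comparison: "To inform future barometer surveys and to generate panel data to track trends in the key implementation domains". It also says the aim is to learn which mode works best at each level.

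Under Quantitative data, "The likert scale-type options will be used for key measures of implementation status". Under Data analysis and displays, all collected data feed the barometer metrics, and "A dashboard or score card will be developed to display performance or progress of the first wave barometer assessment". That section also promises that "All indicators will be tested for validity and reliability", but it does not mention mode. Study limitations does not mention mode either.

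Mode is allocated in two ways. At national level, 120 respondents (40 per policy area) are split half and half at random. Below national level, whole districts are randomised, five to each mode.

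**The concern.** The comparison is meant to guide the choice of mode for a survey whose main product is a set of scores. Whether the two modes give the same scores is therefore central to that choice, and it is the one outcome absent from both lists.

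A shift is plausible, although the documents do not show one. First-order respondents include people with a formal mandate to implement the policies. They rate implementation either to a research assistant in person or alone through a web link. On-line respondents also receive a token payment, and none is mentioned for the others.

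Two uses of the data are exposed:

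- **Trends.** If the mode mix changes after wave 1, part of the apparent change in implementation would be a change of mode.
- **District contrasts.** Because a district has a single mode, a wave 1 contrast between an on-line and a face-to-face district cannot separate mode from implementation.

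**Working it through.** **What the plan fixes.** Taken together, the two lists cover response rate, completeness, costs and ease of access. Neither includes the scores or their distribution. The nearest safeguard, the validity and reliability testing, is generic and names no check by mode.

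**Inputs from the documents.** The total is 570 respondents ("it is anticipated that a total of 570 respondents will be interviewed at national, district, and facility levels"), and 120 + 200 + 250 = 570 reproduces it. The mode rows of Table 3 give 60 + 100 + 125 = 285 per mode. The printed per-mode total of 235 is a separate slip, and nothing here depends on it. Allocation by district covers 200 + 250 = 450 of the 570, that is 450/10 = 45 per district and 5 × 45 = 225 per mode. The documents state no alpha, power, effect size, SD or ICC.

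**Assumptions.** Two-sided alpha 0.05, 80% power, full response, effects in SD units, ICC 0.01 to 0.10, and for illustration a mode shift of 0.2 to 0.4 SD.

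**1. Effect on trends.** Let the shift be δ. In a half-and-half wave the pooled score contains 0.5δ. In a wave using one mode only it contains δ or 0. The false change between the two is 0.5δ in size: 0.5 × 0.2 = 0.1 SD and 0.5 × 0.4 = 0.2 SD. If the mix stays the same and δ is constant, the false change is 0.

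**2. Effect on district contrasts in wave 1.** An on-line district contains δ and a face-to-face district contains 0. The contrast carries the whole of δ, here 0.2 to 0.4 SD.

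**3. Detectable shift at national level.** (1.96 + 0.84) × √(2/60) = 2.80 × 0.1826 = 0.51 SD. Power for shifts of 0.2, 0.3 and 0.5 SD is 19%, 38% and 78%.

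**4. Detectable shift at district and facility level.** The design effect is DE = 1 + (45 − 1) × ICC. With ten districts there are 8 degrees of freedom, so the detectable shift is approximately (2.306 + 0.889) × √(2 × DE/225).

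| Assumed ICC | DE | Detectable shift (SD) | Power for 0.3 SD |
|---|---|---|---|
| 0.01 | 1.44 | 0.36 | 64% |
| 0.05 | 3.20 | 0.54 | 35% |
| 0.10 | 5.40 | 0.70 | 23% |

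Treating all 570 as individually randomised would make the comparison look more precise than this. It would not fit the design, because 450 of them are allocated by district.

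**The case against.** - **The lists may be shorthand.** They differ from each other, the restated objective has none, and an article may leave detail to a fuller document. This has some force. However, the article chose to name the outcomes twice and tied the comparison to trend tracking, and neither list serves that purpose without the scores.
- **A reader might infer that a mode effect must go undetected.** The documents do not support that. Mode is known from the allocation and scores are collected under both modes, so the comparison remains possible at any time. It is simply not planned.
- **A reader might infer that future trends will be biased.** That is also too strong. Under Study design, "Data collection will utilise the same tools and approaches in order to capture any changes", and with an unchanged mix a constant shift largely cancels in overall trends. The bias arises only if the mix changes. That is a real possibility, since the comparison is meant to inform later surveys and the Discussion expects the use of on-line tools to be refined, but it is not the stated plan.
- **District contrasts are not a named output.** The analysis section names comparison by policy or programme area. Both modes occur within every policy area at national level, so a shift common to the three policies would largely cancel between them. The district concern therefore applies only where such contrasts are drawn.
- **Precision is low.** This stands. At an ICC of 0.05 or more, and at national level, the detectable shift exceeds the assumed 0.2 to 0.4 SD. It is a reason to report intervals and not to adjust scores mechanically. It does not justify leaving the comparison out.

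**Conclusion.** The concern holds in a limited form. The named outcomes of objective 4 omit the barometer's key measure, so the plan as written could settle the mode for later waves without evidence on whether the modes agree on the scores. The generic validity testing does not close this gap.

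The possible bias is half the shift in a pooled trend if a half-and-half wave is followed by a single-mode wave, and the whole shift in a wave 1 contrast between districts of different mode. The 0.2 to 0.4 SD shift is an assumption, and nothing in the documents shows that a shift exists.

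The data can detect only fairly large differences: about 0.51 SD at national level, and about 0.36 to 0.70 SD below it, depending on an assumed ICC of 0.01 to 0.10. Full response is assumed throughout, so non-response would make these figures larger.

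**What to change.** 1. Add to objective 4 the between-mode difference in each Likert module score, with a 95% CI.
2. Estimate it separately at national level (60 vs 60, randomised within policy area) and at district and facility level, with the district as the unit of allocation (5 vs 5).
3. Show score-card values by mode as well as pooled.
4. State that a non-significant difference will not be read as equivalence of the modes.
5. Before changing the mode mix in later waves, take the estimated difference and its uncertainty into account. Standardising scores to one mode, or using the estimate as a bridge between waves, should not be required: below national level the estimate rests on ten districts and could add more noise than the bias it removes.

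The cost is a little extra analysis on data already being collected, with no extra fieldwork. The drawback is wide intervals at district level, which the report should state openly.

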##### At national level

respondents will be randomised by policy cluster (e.g. malaria, Family planning and emergency obstetric care). As we target to interview 120 persons at the national level i.e. 40 agencies/departments in each policy area, random allocation will be done to assign half to face-to-face interviews and half to on-line interviews. Before the random allocation, we will organise the second order organisations according to three policy domains to ensure a more balanced response across the three policy areas.

##### At district level

Overall 10 districts will be selected from district clusters (strata) ranked in accordance with the district league table and will be shared with Ministry of Health during the inception stage of the survey. Following this general framework, the selection criteria below was generated and followed in the selection of the districts:i.Top fifteen performing districts according to the following clusters: national, regional, hard- to-reach districts, new districts and districts without regional referral hospitals,ii.Bottom fifteen performing districts in the same clusters in criteria (i) above,iii.Old districts expected to have fairly resilient health systems,iv.Peri – urban versus rural districts, andv.Districts where MakSPH has previously or is currently conducting activities with potential synergies with the PIB.

Using the above criteria, the districts selected to participate in this survey are: Arua, Jinja, Tororo, Hoima, Gulu, Kabarole, Kibuku, Kitgum, Ibanda and Wakiso.

Since there are 10 targeted districts for the PIB, respondents will be randomized using the district as a cluster – 5 districts for online and 5 district for face-to-face interviews. In addition to administration of the questionnaire at the district level, relevant routine data that cannot be collected at the national level will be also be collected.

The face-to-face survey will be conducted in 5 districts to be randomly selected from the 10 selected districts. The remaining districts will be assigned to on-line survey. In each district, interviews will target about 20 district level managers, and 20–25 facility level managers. In total (Table 3), we expect a sample of 570 respondents at the different levels of implementation.

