## Background

Policy implementation remains an under researched area in most countries and it is not surprising that several policies are implemented without a systematic follow up of why and how they are working or failing [1, 2]. It is for this reason that a project entitled “Supporting Policy Engagement for Evidence-based Decisions (SPEED) for Universal Health Coverage (UHC) in Uganda” was launched by the School of Public Health at Makerere University (MakSPH) in 2015. The overall objective of SPEED Project is to strengthen capacity for policy analysis, implementation monitoring and analysis of impact and thereby contribute to accelerating progress towards UHC in Uganda. This paper describes the proposed Policy Implementation Barometer (PIB) survey which is a mechanism to reveal gaps in policy implementation and thereby provide feedback to the decision makers about the implementation of a selected set of policy programmes for UHC. The feedback mechanism will include policy engagements to foster corrective action in areas where such is required. The SPEED project seeks to conduct 3 barometer surveys over its 5 year life span (2015–2020). Lessons from the first wave will advise the implementation of the policies, hence a second barometer survey using the same tools and approach will be conducted in the third years to evaluate progress and change in the implementation of the policies. Finally, the last barometer wave will be conducted in the fifth year, which is the final year of the project. By using the same tools and methods, this evaluation will detect the overall outcomes of the project.

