#### Primary data

Both qualitative and qualitative data will be collected through a structured questionnaire with open and close ended questions administered to relevant stakeholders at macro, meso and micro-level of policy implementation (Table 3). The face-to-face collection of primary data will be facilitated by research assistants who will be trained on how to administer the questionnaires. Five research assistants will be deployed in each district. After completion at facility and district level, a selected number of research assistants from this pool will be assigned to conduct the interviews at national level.

**Table 3 Tab3:** Sample size estimates of key informants at various targeted levels

Data modules	Data source (10 districts) for the first round.	Overall sample size	Country specific sample sizes			
			National	District	Facility	Documents & HMIS-2 data
	*Study units*		*3 policy Areas*	*10 districts*	*50 facilities*	
	*Participants*					
Policy specific module 1. Malaria 2. Emergency obstetric care 3. Family planning	MOH programme officials National programmes DHMT and CSOs In-charge of facilities Programme managers in projects Health workers with related policy experience/roles	170	120 (40 per policy domain)	200 (20 per district	250 (at least 3 persons per facility)	• Programme documents • Policy documents • HMIS trends in the last 2 yrs. • Evaluations documents • Published literature • Government reports • Likert scale interviews with some open-ended questions • 6 modules of questions
Total unique respondents		570	120	200	250	
*Face-to-face interviews*		235	60	100	125	
*On-line interviews*		235	60	100	125	

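### Some districts were chosen for extreme league-table rank, and change is then read without a comparator, so regression to the mean may distort trends in routine indicators.

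*Protocol article*

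**What the plan says.** Under the heading At district level, the protocol article states: "Overall 10 districts will be selected from district clusters (strata) ranked in accordance with the district league table". Five criteria follow.

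- Two are extremes of rank: "Top fifteen performing districts according to the following clusters" and "Bottom fifteen performing districts in the same clusters in criteria (i) above". The clusters are national, regional, hard-to-reach, new, and without a regional referral hospital.
- Three are not: "Old districts expected to have fairly resilient health systems", "Peri – urban versus rural districts", and existing activity of the host institution in the district.

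Ten districts are then named. The criterion that each one met is not given, nor is the year of the league table.

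On change over time, the Background says that the second wave is "to evaluate progress and change in the implementation of the policies". Study design says: "Data collection will utilise the same tools and approaches in order to capture any changes". The section on questionnaire administration speaks of panel data for trends. Table 3 also lists "HMIS trends in the last 2 yrs" among the data for the first round.

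Under Quantitative data, the key measures of implementation status are Likert items. Data analysis and displays builds the barometer metrics from primary and secondary sources together and reports progress by policy or programme area. Study limitations does not mention selection on rank. It does bring in secondary information from many more districts, but to make up for missed context and actors, not as a comparator for change.

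**The concern.** A district's league-table position reflects its lasting performance plus transient error: a bad reporting year, a stock-out, a data-quality problem. Districts picked because they rank very high or very low tend to have transient error in that direction. When they are measured again, they move towards the average even if implementation has not changed.

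If that movement falls inside the interval over which the study reads change, bottom-list districts appear to improve and top-list districts appear to decline. The article describes no comparison group, and the last wave is meant to show the outcomes of the project. Rebound could then be credited to the barometer's feedback and passed to decision makers as progress.

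Routine indicators are the exposed part. They come from the reporting system retrospectively, so their two-year window can cover the period on which districts were ranked. The direction depends on where the ranking period lies: at the start of the window it gives a spurious rise in bottom districts, and at the end it can give a spurious fall.

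**Working it through.** The plan states no SD, reliability, effect size or power for this point, so there is no figure of its own to reproduce. What follows uses assumed inputs to show the possible range.

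**Assumptions (none is in the article).** There are 112 districts in one ranked list. Score = true level + transient error, with total SD 1. Reliability R (share of variance that is lasting) is 0.5, 0.7 or 0.9. Error autocorrelation from league table to wave 1 is ρ = 0, 0.3 or 0.6, and from wave 1 to wave 2 it is ρ², because the gap is longer. There is no true change. Both waves are put on the league-table scale, which is the case most favourable to the concern.

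**Step 1. How extreme the groups are.** In simulation (4,000 replicates), the bottom fifteen average z = 1.59 SD below the mean, and the top fifteen lie as far above it.

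**Step 2. Ranked score used as baseline, independent errors.** Shift = z(1 − R):

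- R = 0.5: 1.59 × 0.5 = 0.80 SD
- R = 0.7: 1.59 × 0.3 = 0.48 SD
- R = 0.9: 1.59 × 0.1 = 0.16 SD

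The simulation agrees (0.80, 0.48, 0.16).

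**Step 3. Wave 1 used as baseline.** This is the plan's wave-to-wave comparison. At wave 1 the group's expected transient error is z(1 − R)ρ, and at wave 2 it is z(1 − R)ρ × ρ². The spurious change is the difference, z(1 − R)ρ(1 − ρ²).

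| R | ρ = 0 | ρ = 0.3 | ρ = 0.6 |
|---|---|---|---|
| 0.5 | 0.00 | 1.59 × 0.5 × 0.273 = 0.22 | 1.59 × 0.5 × 0.384 = 0.31 |
| 0.7 | 0.00 | 1.59 × 0.3 × 0.273 = 0.13 | 1.59 × 0.3 × 0.384 = 0.18 |
| 0.9 | 0.00 | 1.59 × 0.1 × 0.273 = 0.04 | 1.59 × 0.1 × 0.384 = 0.06 |

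For ρ above zero, the simulated rises in the bottom group are 0.21 and 0.31, 0.13 and 0.18, and 0.05 and 0.06. The top group falls by about the same amounts. With independent errors the whole regression happens before wave 1, and nothing is left for the wave 1 to wave 2 change.

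**Step 4. Pooling the ten districts.** With b bottom-list and t top-list districts, the pooled shift is (b − t)/10 times the group shift. With b = t it is zero, as simulated in every scenario. With an illustrative 7 and 3, the factor is 0.4, and the pooled shift is 0.4 × 0.05 = 0.02 to 0.4 × 0.31 = 0.12 SD. Districts chosen on the other three criteria dilute it further.

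**Step 5. Smaller clusters.** Fifteen out of 30 is only 0.77 SD from the mean. All the shifts above then shrink by 0.77/1.59, to about half.

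**Step 6. Which measure is in which case.** The Likert scores are new measurements made after selection with a different instrument, so they sit near the ρ = 0 column. Routine indicators may share inputs and period with the league table. A window that opens in the ranking period puts them near step 2, to the extent that the indicator shares the ranked score's error.

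**The case against.** The strongest reply is that regression to the mean biases change only when the selection measurement is also the baseline or shares its transient error. Here change across waves starts from a separate wave 1, and step 3 gives 0.00 SD with independent errors. That stands, and it largely clears the Likert scores.

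Other parts of the reply also stand. Three of the five criteria are not rank extremes. A top or bottom fifteen within a small cluster need not be extreme. Progress is to be shown by policy area, and no contrast of top against bottom districts is planned. National respondents, 120 of 570, are not subject to district selection. Nothing says outright that the same ten districts return, although the longitudinal and panel language points that way. Overlap between the league table and the routine-data window is possible but not stated.

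What does not stand is the view that nothing remains. The routine data are retrospective, so the protection of a post-selection baseline does not extend to the two-year look-back. Cancellation by pooling needs equal numbers from the two lists, and the article does not give them. The secondary data from other districts could serve as a comparator but are not assigned that role. The abstract's statement that the districts were randomly selected does not help either: it conflicts with the listed criteria, and a random draw from within the extreme lists would regress in the same way.

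A reader might infer that bottom districts will show false progress and top districts false decline, by up to about 0.8 SD. The documents do not support that. It would need the ranked score, or something carrying all of its error, to be the baseline, and the article nowhere says so.

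**Conclusion.** The concern holds as a conditional, unaddressed risk that is confined mainly to routine DHIS-2/HMIS indicators. It matters if their baseline period overlaps the ranking period, and it becomes visible if change is read district by district or if the top and bottom lists are unequally represented.

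Under the assumptions above, the spurious wave 1 to wave 2 change is about 0.05 to 0.31 SD per group when some transient error carries over. It is zero when errors are independent or when equal numbers are pooled. The range of 0.16 to 0.80 SD applies only if the ranked score is itself the baseline. The number of districts, the reliability, the carry-over, the mix of lists and the return of the same districts are all assumptions, so these figures show scale and are not estimates for this study.

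**What to change.** 1. **At district level:** state which criterion or criteria each of the ten districts met, and the period that the league table covers.
2. **Data analysis and displays:** take the baseline for routine indicators from a period not used for the ranking. Report change in the ten districts as the difference from the all-district DHIS-2 change over the same period. The two parts do different work. The baseline period deals with regression, while the all-district difference removes the trend common to all districts and would not remove regression by itself.
3. **Study limitations:** add that convergence of top- and bottom-ranked districts on routine indicators is not, taken alone, evidence of effect.

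Adjusting change for the league-table score is not advisable: with ten districts the adjustment could barely be estimated.

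The cost is some wording and one further extract from a system already in use. The downside is that some apparent progress may shrink.
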